## Abstract

**Background:**

Sleep disorders are common and costly to society. Guidelines from the American Academy of Sleep Medicine (AASM) and the Australasian Sleep Association (ASA) recommend Cognitive Behaviour Therapy for Insomnia (CBTi) as the best treatment modality for insomnia disorder in the long term, however, access issues due to medical first referral pathways and psychology workforce shortages in the community result in increased wait times, reduces efficient care for patients, and adds burden to specialist medical services.

**Method:**

This single-site, multiphase, mixed methods study will implement and evaluate a service model of care re-design incorporating a new Direct to Psychology referral pathway for insomnia presentations and a Stepped Care treatment approach including digital intervention in a quaternary public multidisciplinary sleep service. The RE-AIM framework and Standards for intervention Reporting Implementation Studies (StaRI) will be used to guide the development, implementation, evaluation and reporting of this service change. Quantitative data measuring outcomes of the new models of care on key indices of patient clinical outcomes, patient/clinician service satisfaction, and service efficiencies will be collected pre- and post-service change.

**Discussion:**

The overarching aim of this project is implement and evaluate a model of care change to the service model in a public tertiary hospital multidisciplinary sleep service. The new Direct to Psychology Stepped Care Model incorporates a Direct to Psychology Insomnia referral pathway along with a Stepped Care approach to treatment, flexibly delivered across the continuum of care. The project will measure the impact of the service change in our target population. The new model of care will be compared to the old service model for key outcomes. We anticipate that the new Model of Care will be acceptable to stakeholders, will produce non-inferior patient outcomes and experience, and will improve patient flow and service efficiency.

**Trial registration:**

The Protocol was registered on 5/08/2022 with the Australian and New Zealand Clinical Trials Registry (ACTRN12622001086752). The study was conducted in accordance with the protocol version 4: 12 March 2024.

**Supplementary Information:**

The online version contains supplementary material available at 10.1186/s12913-025-13134-5.

## Background

Insomnia is one of the most common sleep disorders globally [1, 2], with up to 15% of the population diagnosed every year. The total health system cost in Australia due to sleep disorders was estimated to be $0.9 billion in 2019-20, 30% of which was attributable to insomnia [3]. Insomnia is a direct predictor of the development and exacerbation of mental health disorders [4], and psychological treatment of insomnia is associated with improved mental health outcomes and prevention of relapse in the case of comorbid depression [5] and anxiety, even if the depression or anxiety itself is not targeted for intervention [5, 6]. In the case of comorbid insomnia and Obstructive Sleep Apnoea (OSA) (COMISA), psychological intervention for insomnia is associated with significantly increased acceptance and adherence to Continuous Positive Airway Pressure therapy (CPAP), the gold standard treatment for OSA [7].

Sleep Psychology is a necessary resource within any sleep disorders service, with AASM guidelines recommending a Psychologist with experience in behavioural sleep medicine be embedded in multidisciplinary sleep services [8]. However, barriers to patient access to treatment include limited availability of appropriately trained and experienced psychologists [9] and lack of knowledge amongst primary practitioners about evidence-based treatment for insomnia [10]. To this end, it is important to explore options for improving efficiencies and access to care for individuals requiring intervention.

There is significant evidence for Cognitive Behaviour Therapy for insomnia (CBTi) as the first-line treatment for insomnia [2, 11], recommended by both the American Academy of Sleep Medicine (AASM) and the Australasian Sleep Association (ASA), as CBTi has extensive Level I evidence for longitudinal gains in insomnia resolution [8, 12]. Internet-delivered CBTi has been extensively investigated in the clinical literature, with systematic reviews and meta-analyses demonstrating that these first-line interventions are just as effective as face-to-face modalities in the general population for those with insomnia of low to moderate severity [6, 13–18]. “Stepped care” refers to a service delivery model allowing a relatively scarce healthcare resource to be applied in a cost-effective way to achieve timely and effective clinical care [15, 19]. CBTi is a well validated intervention with demonstrated amenability to a Stepped Care model, where patients are assessed for entry to first-line manualised and online treatment programs, increasing to progressively more time, cost and expertise intensive levels ‘upstream’ where there is an incomplete therapeutic response to a first-line intervention, or when clinical complexity demands a more intensive intervention step within the care pathway.

In our tertiary public hospital multidisciplinary sleep service, the current model of care (MoC) relies on a “medical-first” referral pathway which overburdens specialist medical services and delays care to evidence-based psychological treatment. Furthermore, intensive 1:1 interventions with the sleep psychology team results in bottlenecks in patient access. These pressures require implementation of systematised and innovative models of care, delegation to junior staff, and utilisation of time efficient (e.g., group delivery) and technological solutions designed to improve service efficiencies, effectiveness of care, and to maintain or improve patient reported experience and outcomes. A protocol for the evaluation of a new Direct to Psychology Stepped Care Model to address these pressures is presented, which utilises a direct referral pathway as well as stepped care approaches to service delivery. This study has a particular interest in exploring the feasibility and acceptability of digital intervention as a first-line treatment option.

## Methods

### Aims and objectives

The overarching aim of the current study is to evaluate the impact of adopting a new Direct to Psychology Stepped Care Model into the multidisciplinary sleep service. The model of care will incorporate a “Direct to Psychology Insomnia” referral pathway, with a “Stepped Care” treatment approach that utilises digital, group, trainee and clinician level interventions, flexibly delivered across the continuum of care. The RE-AIM Framework [20, 21] will be adopted to evaluate individual and service level outcomes in a pre- post study design comparing Standard Care to Direct to Psychology Stepped Care. The objective is to capture all service events, clinical outcomes and quality of life changes for patients referred to the sleep psychology service in order to perform a full evaluation including a cost effectiveness analysis.

The specific hypotheses include the following:

Compared to Standard Care, the Direct to Psychology Stepped Care Model will be associated with:Reduced wait times and improved access to treatmentEquivalent (non-inferior) clinical outcomes and changes in quality of lifeService delivery that is less resource intensive and delivered at a lower cost

In addition, we hypothesize that stakeholders (referrer, patient, staff) will be satisfied with the service changes.

### Design and setting

This project will employ a single-site, multi-phase, mixed-methods approach to evaluate the implementation of the new model of care into the Sleep Psychology service in a tertiary public hospital, embedded within the RE-AIM implementation evaluation framework [19, 20, 22]. Reporting will align with the Standards for intervention Reporting Implementation Studies (STaRI) framework [23]. Patient, service-level and implementation outcomes will be evaluated by comparing patients attending the service from 1 January 2021 until 30 June 2023 as a pre-measure (old model of care) to patients attending the service from implementation of the model from 1 July 2023 to 31 December 2024 as a post-measure (new model of care). This project has received ethics approval via the low and negligible risk pathway with a waiver of informed consent with the Darling Downs Human Research Ethics Committee (HREC 2022 QTDD 88350). Figure 1 outlines the study flow.

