#### Patients

Consecutive patients attending the Sleep Psychology service from 1 January 2021. Inclusion criteria will include all NEW patient referrals to the Sleep Disorders Service at the Prince Charles Hospital in Brisbane, Australia who would have been referred to Sleep Psychology at some point in their patient journey from 1 January 2021 until 31 December 2024. Data collection will continue until December 2025 as patients filter through the treatment model. Exclusion criteria will include any patients referred prior to 1 January 2021 or after completion of the study.

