*How effective was the model of care in achieving its intended outcomes?*	**Effectiveness** – impact on outcomes and quality of life/economic outcomes	**Primary outcomes** *Service Access Measures* • Average number of occasions of Service within Sleep Psychology service under ‘old’ model compared to ‘new’ model of care • Percentage of new patient activity under ‘old’ model compared to ‘new’ model of care • Average wait-time to access a first appointment with Sleep Psychology from date of referral under ‘old’ model compared to ‘new’ model of care • Average time to discharge from first appointment to final appointment with Sleep Psychology under ‘old’ model compared to ‘new’ model of care • Percentage of patients discharged from psychology *Patient-related Outcomes* • Change scores on clinical outcome measures pre- to post- treatment on clinical outcome measures (ISI, DASS-21, K10 and EQ-5D-5 L) comparing patients treated under ‘old’ model versus ‘new’ model of care • % patients treated adequately at each level of Stepped Care • Differences in patient characteristics (age, sex, geographical location, presenting issue) between those who are adequately treated at each level of the new model of care (moderation analysis) *Economic Outcomes* • Quality-adjusted life year calculations as a measure of cost-effectiveness of the ‘new’ model of care compared to the ‘old’ model of standard care **Secondary outcomes** *Patient satisfaction* • Patient satisfaction measure (SRS) post- treatment comparing patients treated under ‘old’ model versus ‘new’ model of care *Patient satisfaction with digital intervention* • Patient reported ease of access to digital intervention • Acceptability and relatability of the online program/service provided (rated by patients), including: i. motivation to access online treatment (diversion from public hospital services for insomnia treatment) ii. understanding of intervention materials iv. perceived change in sleep problem • Differences in patient characteristics (age, sex, geographical location, presenting issue) between those who complete the digital intervention compared to those who do not complete	Significantly fewer occasions of service under new model of care Significantly greater % new patient appointments under new model Significantly shorter wait-time to first appointment under new model Significantly shorter time to discharge under new model Outcomes are non-inferior under new model of care; upper bound 95%CI on outcome measures is less than MCID MCID is achieved on outcome measures by > 80% patients at each level The ‘new’ model is more cost effective Patient reported satisfaction is non-inferior under new model of care; upper bound 95%CI is less than MCID > 90% patients report positive experiences	Patient qualitative and quantitative surveys Medical Record Patient registration system

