### Statistical analysis

The project will employ a mixed methods approach. Qualitative surveys for patients, multidisciplinary staff, and referrers was undertaken pre-service change to ascertain the acceptability of the digital therapy, as well as familiarity, access, confidence, and relatability of this treatment option [25]. Post-implementation surveys will also be undertaken on these same metrics. Quantitative data will be collected pre- and post-service change to ascertain treatment effectiveness in terms of clinical outcome measures, as well as service measures of interest such as patient flow, occasions of service and program engagement. Based on similar studies [40], and allowing for some incomplete data, we expect to have data for approximately 110 participants from each pre- and post- time period, resulting in a sample of 220 participants overall who will be suitable for the Direct to Psychology pathway. To assess wait times, participants will be categorised into four groups based on the time-period (pre/post implementation) and whether they met eligibility criteria for the Direct to Psychology pathway. Differences in wait times between the groups will be assessed using a one-way Analysis of Variance (ANOVA) and linear regression modelling. In a one-way ANOVA study, a sample of 220 participants, divided by 4 groups, achieves 80% power with a significance level of 0.05 to detect a moderate-large effect size (Cohen’s f) of 0.25 [41]. The effects of other variables of interest and potential confounders (patient characteristics, diagnosis,) will be tested in multivariable models. For differences in patient outcome measures pre- and post- intervention when comparing pre- and post- service change, the mean between-group difference and 95% confidence interval (CI) will be calculated. As this aspect of the evaluation is a non-inferiority trial (that is, we expect clinical outcomes to not be reduced due to the service change), the criteria adopted to determine non-inferiority will be if the upper bound 95%CI on each clinical outcome measure was less than the minimal clinical important difference (MCID). Quantitative data measuring pre- and post- service change outcomes on key indices of patient service satisfaction, service characteristics (e.g., occasions of service); as well as referrer and staff service satisfaction, and engagement with digital therapies, will be evaluated via univariate statistical tests where indicated such as independent samples t-test (or nonparametric equivalent), and categorical comparisons will be evaluated using Pearson’s chi-square. The distribution of outcome measures will be assessed, and appropriate transformations will be applied for use in modelling. Differences between group means will be tested using generalised linear regression modelling. Health related quality of life will be measured pre- and post- implementation using the EQ-5D-5 L. Population norms for EQ-5D-5 L Australia will be used to value the data set [42].

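### Splitting old and new model by attendance date, with referrals before January 2021 excluded, makes new-model waits look longer even if the model changes nothing

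*Protocol article*

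**What the plan says.** Design and setting defines the comparison by attendance. The old model is "comparing patients attending the service from 1 January 2021 until 30 June 2023 as a pre-measure (old model of care"), a window of 30 months. The new model is "patients attending the service from implementation of the model from 1 July 2023 to 31 December 2024 as a post-measure (new model of care"), a window of 18 months.

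The Patients section also opens with attendance ("Consecutive patients attending the Sleep Psychology service from 1 January 2021"), but then sets eligibility by referral: new referrals "who would have been referred to Sleep Psychology at some point in their patient journey from 1 January 2021 until 31 December 2024". It adds: "Exclusion criteria will include any patients referred prior to 1 January 2021 or after completion of the study". On follow-up it says: "Data collection will continue until December 2025 as patients filter through the treatment model".

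Table 1 (RE-AIM) lists as a primary outcome "Average wait-time to access a first appointment with Sleep Psychology from date of referral", compared between old and new model, and sets a significantly shorter wait as the standard. In the Statistical analysis section participants are grouped by period (before or after implementation) and by eligibility for the direct pathway, and "Differences in wait times between the groups will be assessed using a one-way Analysis of Variance (ANOVA) and linear regression modelling". That section does not say which date places a patient in a period.

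**The concern.** A wait starts at referral and ends at attendance. If the cohort is chosen by when the wait ends, while nobody whose wait began before 1 January 2021 is admitted, the longest wait that can be observed depends on the calendar. Someone attending in March 2021 can show a wait of three months at most. Someone attending in December 2024 can show almost four years.

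The attendance rule also places in the new model everyone who queued under the old one. A patient referred in March 2023 and first seen in September 2023 counts as a new-model wait. Yet the Intervention section has referrals directed to a pathway at triage, so as far as the text shows this patient was triaged before the new pathway existed.

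Reduced waiting is the first hypothesis, a primary outcome, and the only outcome for which the article gives a power calculation. A comparison of mean observed waits would mix the effect of the model with the effect of the windows.

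**Working it through.** **The plan's own figure.** The article states 80% power for N = 220, four groups, f = 0.25 and alpha 0.05. With noncentrality 220 × 0.25² = 13.75 and 3 and 216 degrees of freedom, the power is 88.4%. The stated figure is conservative and has no bearing on this point.

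**Inputs from the article, in months from 1 January 2021.** First eligible referral 0; go-live 30; last referral and end of the new-model window 48; end of data collection 60.

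**Assumptions, because the article gives no wait data.** Constant referral rate; the same wait distribution in both periods, so the true effect is zero; mean wait 3, 6 or 12 months; exponential or, less spread out, gamma with shape 4.

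**Caps.** An old-model attender is referred at 0 or later and seen before 30, so the wait is below 30. A new-model attender is seen before 48, so the wait is below 48.

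**Exponential waits with mean m, closed form.** Per unit referral rate, the number seen by time T is D(T) = T − m(1 − e^(−T/m)). The sum of their waits is N(T) = mT − 2m²(1 − e^(−T/m)) + mT·e^(−T/m). The old mean is N(30)/D(30), and the new mean is [N(48) − N(30)]/[D(48) − D(30)].

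- m = 6: old 109.70/24.04 = 4.56; new (216.12 − 109.70)/(42.00 − 24.04) = 5.93.
- m = 12: old 125.19/18.99 = 6.59; new (303.82 − 125.19)/(36.22 − 18.99) = 10.37.

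The share of new-model attenders referred before go-live is 1 − D(18)/[D(48) − D(30)]. For m = 6 this is 1 − 12.30/17.96 = 32%; for m = 12 it is 1 − 8.68/17.23 = 50%. At m = 3 it is 17%, close to 3/18. The shares for gamma waits are similar at 3 and 6 months and higher at 12.

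**Attendance split, simulated** (second decimals differ slightly from the closed form). The last column is the chance that a two-sided 5% comparison of 110 with 110 is significant under no effect. It is a two-group approximation to the planned four-group test.

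| Mean wait | Distribution | Old | New | Difference | d | False-positive rate |
|---|---|---|---|---|---|---|
| 3 | exponential | 2.67 | 3.00 | +0.33 | 0.12 | 14% |
| 3 | gamma | 2.92 | 3.00 | +0.08 | 0.06 | 7% |
| 6 | exponential | 4.57 | 5.92 | +1.35 | 0.27 | 50% |
| 6 | gamma | 5.62 | 6.00 | +0.38 | 0.13 | 16% |
| 12 | exponential | 6.60 | 10.36 | +3.76 | 0.50 | 96% |
| 12 | gamma | 10.06 | 11.94 | +1.89 | 0.36 | 75% |

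**Referral split, averaging only waits observed by December 2025.** Old-model follow-up is 60 − 30 = 30 to 60 months; new-model follow-up is 60 − 48 = 12 to 60 − 30 = 30. Long new-model waits go unseen and the sign reverses. The exponential differences are −0.05, −0.72 and −3.19 months at means of 3, 6 and 12. The gamma differences are 0.00, −0.04 and −1.33.

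**Referral split, restricted mean wait to 12 months.** At an exponential mean of 12, old is 7.58 and new 7.59, with a false-positive rate of 5.0%. With old-model patients censored at go-live as well, the two restricted means agree within 0.04 months.

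**Time from first to final appointment.** With cohorts by first appointment and only treatment completed by December 2025 counted, the null bias is −1.5%, −12%, −22.5% and −30% for assumed mean durations of 3, 6, 9 and 12 months.

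**The case against.** A reader might infer that the article gives two rival definitions of old and new, so that the sign of the bias depends on which section is followed. The text does not support that. The Patients section sets eligibility and a start date and nowhere draws the old/new boundary. The only split stated is by attendance. Admission by referral date combined with allocation by attendance is one rule. The reversed sign belongs to a reading that no section prescribes, though the Statistical analysis section leaves it open.

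A reader might also infer that the design manufactures the hoped-for benefit on waits. Under the stated rule the bias runs against the new model, so it could hide a real reduction.

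The size rests on an assumed wait and is small at about 3 months. Comparing d = 0.50 with the planned f = 0.25 is exact only if the four group means split two against two. These limits stand.

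It is tempting to say that time to discharge is truncated in the same way. Table 1 measures it from first to final appointment. Its bias runs in the opposite direction to the wait bias and is slight for short treatment. Occasions of service were not calculated.

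Finally, the handling of patients not yet seen can be left to an analysis plan, and the study-flow figure is not shown. But the windows, the referral cut-off and the analysis of observed waits are fixed in the article, and they produce the error when followed as written.

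**Conclusion.** The point holds for wait time. Followed as written, the plan gives a biased comparison on a primary outcome, and the direction under the stated rule is known: new-model waits look too long. With no true effect the excess is about 0.1 to 0.3 months at an assumed mean wait of 3 months, 0.4 to 1.4 at 6 and 1.9 to 3.8 at 12, with d up to 0.50. The share of new-model attenders who queued before go-live is about 17%, 32% and 50% or more respectively.

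The existence and sign of the bias follow from the article's dates, given steady referrals. Its size depends on the wait distribution, which the article does not report. Switching to a referral split alone is no cure. If only observed waits are averaged, the error reverses: about 0 at 3 months, up to −0.7 at 6 and up to −3.2 at 12.

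**What to change.** For the wait-time outcome only:

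- Set the period by date of referral, before or from 1 July 2023, and say so in the Statistical analysis section.
- Analyse referral to first psychology appointment, or to treatment start, as time to event: Kaplan-Meier curves, adjusted regression, and restricted mean wait to 12 months. Every eligible referral has that horizon if data run to the end of December 2025.
- Keep patients not yet seen as censored, and censor old-model patients still waiting at 1 July 2023.

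For clinical outcomes, satisfaction and occasions of service, keep grouping by the model under which the patient was treated. A referral-date split there would count care given under the new model as old-model care and pull the non-inferiority comparison toward no difference. Compare time from first to final appointment over a common follow-up from first appointment, with undischarged patients censored.

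The cost is a change of analysis wording. Referral date is already needed to measure the wait, so no new data are collected. Two downsides should be stated: waits beyond 12 months contribute only up to 12 months, and the wait and clinical-outcome cohorts will differ by the patients who straddle go-live.
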